## Abstract

**Background:**

There are several protocols designed to treat vestibular disorders that focus on habituation, substitution, adaptation, and compensation exercises. However, protocols that contemplate not only vestibular stimulation but also other components that are essential to the body balance control in older people are rare. This study aims to compare the effectiveness of two vestibular rehabilitation protocols (conventional versus multimodal) on the functional capacity and body balance control of older people with chronic dizziness due to vestibular disorders.

**Methods/design:**

A randomized, single-blind, controlled clinical trial with a 3 months follow-up period will be performed. The sample will be composed of older individuals with a clinical diagnosis of chronic dizziness resulting from vestibular disorders. The subjects will be evaluated at baseline, post-treatment and follow-up. Primary outcomes will be determined in accordance with the Dizziness Handicap Inventory (functional capacity) and the Dynamic Gait Index (body balance). Secondary outcomes include dizziness features, functional records, body balance control tests, and psychological information. The older individuals (minimum sample *n* = 68) will be randomized to either the conventional or multimodal Cawthorne&Cooksey protocols. The protocols will be performed during individual 50-minute sessions, twice a week, for 2 months (a total of 16 sessions). The outcomes of both protocols will be compared according to the intention-to-treat analysis.

**Discussion:**

Vestibular rehabilitation through the Cawthorne&Cooksey protocol has already proved to be effective. However, the addition of other components related to body balance control has been proposed to improve the rehabilitation of older people with chronic dizziness from vestibular disorders.

**Trial registration:**

ACTRN12610000018011

## Background

Aging is characterized by gradual physiological modifications in the body’s systems, which at an advanced age lead to decline of their functions and increased susceptibility to diseases or health disturbances
[1]. Among the various consequences of ageing, dizziness requires special professional attention, since it is related to several etiological factors
[2]. Furthermore, this symptom is highly prevalent at an advanced age
[3], correlates with body unsteadiness and falls
[4,5], and negatively impacts daily activities
[5] and quality of life
[5,6].

Although the dizziness can be attributed to many causes, nearly one-half of these cases are the result of vestibular dysfunction
[6-8]. Vestibular dysfunction is present in 18.5% of adults aged 40 to 49 years, in 49.4% of older people aged 60 to 69 years, and up to 84.8% in older people aged 80 years and older
[9]. Besides being relatively more prevalent at an advanced age, dizziness could be considered even more dangerous in older people
[10], when impairments in other body balance control systems can occur simultaneously
[11].

Vestibular dysfunction is typically characterized by vertigo (a sensation of rotatory motion) or body imbalance (disturbances in gaze and postural stability)
[9,12]. These symptoms are usually triggered during activities that require head movements, transfers, and ambulation. Consequently, vestibular disorders are frequently reported to cause significant discomfort, to reduce independence during daily activities, and to disturb body balance
[9,13].

There are several protocols designed to treat vestibular disorders that focus on habituation, substitution, adaptation, and compensation exercises, recognized as vestibular rehabilitation (VR). In a previous systematic review of the effects of VR on adults and older people with dizziness, it was observed that the Cawthorne&Cooksey protocol was the most common therapeutic approach reported by the selected studies
[14].

In a clinical trial, when older individuals were submitted to VR, the Cawthorne&Cooksey protocol was considered effective at controlling body imbalance in all cases, while the Tusa and Herdman protocol was shown to be effective in 87.5% of cases
[15]. Both protocols reduced disability in the activities of daily living. In another trial, which also submitted older people with body unsteadiness, vertigo or dizziness (*n* = 215) to the Cawthorne&Cooksey protocol, complete improvement in the vestibular symptoms was observed in 19.3% of the sample
[16].

Even though the Cawthorne&Cooksey protocol presents favorable results
[15,16], it still lacks exercises for simultaneous management of the proprioceptive and visual information, modification in the base of support, and other motor components. Other studies with multiple-component rehabilitation protocols (balance, flexibility, and strength exercises) have revealed positive results concerning body balance control and the functional capacity of older people
[17,18].

According to the evidence that body balance control in older people depends not only on the vestibular system, but also on correlations among all the other systems, it has been proposed that the addition of multiple-component exercises might improve Cawthorne&Cooksey protocol effectiveness. There is also reason to believe that a multimodal protocol might increase older people’s independence in daily activities and body balance control, and as a consequence may reduce falls. Moreover, only a few clinical trials have so far investigated the effects of VR on samples composed exclusively of older individuals; and original and better designed trials are still required in order to provide reliable conclusions
[14].

### Aim of the proposed study

This study aims to evaluate and compare the effectiveness of two VR protocols (conventional Cawthorne&Cooksey versus multimodal Cawthorne&Cooksey) concerning functional capacity and body balance control in older people with chronic dizziness derived from vestibular disorders. Secondarily, this clinical trial intends to report sample withdrawals, adverse events and session-to-session VR progress.

## Methods/design

This is a randomized, single-blind, controlled clinical trial with a 3 months follow-up period. The study was approved by the Federal University of São Paulo (UNIFESP) Ethics Review Board (1656/09), and registered in the Australian New Zealand Clinical Trials Registry (ACTRN 12610000018011). The research is reported according to the items stated in the Consolidated Standards of Reporting Trials
[19]. Figure 
1 shows the flowchart for the research.

**Figure 1 F1:**
[figure not shown]
Trial flowchart.

### Sample and setting

The sample will be composed of older individuals with complaints of chronic dizziness resulting from vestibular disorders, indicated by the failure to compensate dizziness 2 months or more after the first occurrence
[20].

The subjects will be referred to the UNIFESP Otoneurology outpatient clinic, which is an interdisciplinary (otolaryngologists, speech therapists, and physiotherapists) treatment center located in the city of São Paulo, Brazil. The Otoneurology outpatient clinic is part of a public health structure, where chronic dizziness complainers are routinely submitted to anamnesis, otolaryngological examination, and hearing and vestibular tests in order to define the dizziness etiology. Following referral and evaluation, those who require VR will have their names included in an official waiting list for subsequent treatment.

### Recruitment

The patients included in the waiting list will receive a telephone call, during which general information regarding VR will be provided, and they will be asked to take part in the research. For those interested in participating, an appointment will be scheduled at the Otoneurology outpatient clinic to determine their eligibility. Those who are eligible will be asked to sign the informed consent and will be submitted to the baseline evaluation. Patients who do not conform to the inclusion criteria or who refused to take part in the study will be referred for rehabilitation outside the research protocol.

### Inclusion and exclusion criteria

The inclusion criteria are: age 65 years old and over, both genders, and clinical diagnosis of chronic dizziness resulting from a vestibular disorder.

Individuals will be excluded in cases of dizziness not resulting from a vestibular disorder, cognitive deficit (reference values according to the Mini-Mental State Examination considering education level
[21]), locomotion requiring a walker or wheelchair, practicing regular physical activities
[22], those who were submitted to VR in the previous 6 months, and those under medication for vestibular disorders. Patients presenting benign paroxystic positional vertigo will be also excluded, since the research protocol does not include repositioning maneuvers.

The occurrence of other chronic and disabling diseases will not be considered an exclusion criterion, in order to obtain a representative sample with proper external validity.

### Randomization

Older individuals who meet the inclusion criteria following the baseline assessment and sign the informed consent will be randomized into one of two VR protocols: conventional or multimodal. Randomization will be accomplished by a statistical computer program, by blocks. The block randomization will be gradually performed during the study according to the number of eligible participants registered on the waiting list. Hence, the block sizes will not be fixed and will vary from 4 to 12 subjects, concerning the minimum and maximum capacity for VR at the Otoneurology outpatient clinic. Blocks will therefore eventually be composed of an odd number of participants, and as a consequence unequal groups could be formed. Block randomization was preferred in order to prevent time-related influences from disturbing the homogeneity of both groups over the data collection period (2 years and 6 months). Sample randomization and allocation will be performed by a researcher who is not involved in the clinical trial. In order to assure concealed allocation, the treating therapist will be informed by telephone call regarding the allocation of each participant just before their first session.

### Blinding

Since both interventions are physical exercises, it will not be possible to blind the patient nor the therapist during this research. Hence, this study must be categorized as single blind, since only the outcome assessor will be unaware of intervention assignment. Even though the patients will be consciously under VR, they will be blinded in relation to the protocol they will be involved in. To evaluate the success of blinding, both the outcome assessor and the subjects will be asked at follow-up assessment to provide their opinion concerning which treatment protocol each of the participants was allocated to.

### Outcome measures

Older patients will be submitted to baseline assessment (prior to randomization), and will be retested at post-treatment (8 weeks) and follow-up (3 months). The primary outcome measure to evaluate functional capacity is the Dizziness Handicap Inventory (DHI), while body balance control will be assessed by the Dynamic Gait Index (DGI).

The DHI is a self-perceived instrument that evaluates the impact of dizziness and unsteadiness on the quality of life of patients with vestibular disorders
[12,23]. The questionnaire consists of 25 items, divided into a seven-item physical subscale, a nine-item emotional subscale and a nine-item functional subscale. The total score ranges from 0 points (no handicap) to 100 points (severe handicap). To analyze DHI results, the total score, the categorical cutoff score >60 points, which indicates severe handicap
[24], and a reduction in the score ≥18 points following treatment, which is considered significant improvement in the quality of life
[25], will all be used.

The DGI is a functional gait scale composed of eight items with varying walking demands (ordinary walking, walking at different speeds, walking with vertical and horizontal head turns, walking over and around objects, making a 180° turn, and stair climbing)
[26,27]. The total score ranges from 0 points (severe impairment) to 24 points (normal performance). To analyze DGI results, the total score, the categorical cutoff score <19 points for fall risk
[28] and an increase in the score ≥4 points to identify a significant improvement following treatment
[25] will be used.

Secondary outcome measures will include the following measures.

Dizziness features will be assessed using a visual analog scale, etiology (peripheral, central vestibular disorder, or both), time elapsed from the first occurrence, duration and frequency, and associated symptoms. Fall data will include the history of falls in the previous 6 months and fear of falling. Hand-grip strength (kg) will be assessed by the manual hydraulics dynamometer SAEHAN™ (SAEHAN Corporation, SH5001, Masan, South Korea).

The Activities-specific Balance Confidence Scale is a self-perceived measure of balance confidence in performing daily activities
[29], with the score ranging from 0% (no confidence) to 100% (complete confidence).

The Vestibular Disorders Activities of Daily Living Scale evaluates the self-perceived impact of vestibular impairment on daily activities
[30]. This scale consists of 28 questions divided into a twelve-item functional subscale, a nine-item ambulation subscale, and a seven-item instrumental subscale. The activities are classified according to a 10-point qualitative scale. The overall and subscales scores are calculated by taking the median values
[31].

The Time Up and Go Test (TUG) is a mobility assessment tool
[32], including versions with a dual task (TUG_cognitive_ and TUG_manual_)
[33-35]. The test quantifies the time taken (seconds) to stand up, walk 3 m, turn, walk back, and sit down.

The Sit-to-Stand Test
[36] is used to measure lower-extremity strength, postural control, and disability in older people and patients with vestibular disorders
[37,38]. The measurement is obtained by the time required (seconds) to stand up and sit down five times, as quickly as possible.

The Multi Directional Functional Reach Test evaluates the limits of stability in the anterior–posterior and medial–lateral directions
[39]. The measurement is obtained through the displacement reached by the patient (cm), shifting the center of gravity to the limits of the base of support while the feet remain stationary.

The static balance, the Romberg, the Romberg on unstable surface, the tandem position and the single leg stance tests
[40,41] will all be tested for 30 seconds with eyes open and with eyes closed. The best time achieved over three trials is recorded.

The Geriatric Depression Scale is a 15-item screening questionnaire for symptoms of depression specifically for the older population
[42,43]. The total score ranges from 0 to 15 points. A cutoff score ≥5 points indicates a depression mood
[43].

Home exercise adherence will be assessed during and after the treatment, using a questionnaire developed by the researchers. Finally, adherence and adverse effects will also be recorded during the treatment sessions.

The following data will be collected at baseline to characterize the sample: social and demographic data (age, sex and education); anthropometric data (weight (kg), height (m), body mass index (kg/m^2^), upper limbs (cm), and feet length (cm)); health status (associated diseases, medication, use of assistive device (cane), complaint of musculoskeletal pain and smoking habit); and the Mini-Mental State Examination
[21,44].

A follow-up questionnaire were developed by the researchers (satisfaction with treatment, hospitalization, unexpected clinical appointments, change in medication, use of medication for dizziness, new clinical diagnosis, occurrence of negative events in life) and will be also applied in order to detect possible problems that could interfere in the VR results in the long term.

The time frame and measures are depicted in Table 
1. The assessments will be performed by trained physiotherapists. Each subject will be evaluated by the same outcome assessor at each time point.

**Table 1 T1:** Measures and time frame

**Measure**	**Baseline**	**Post-treatment****(8 weeks)**	**Follow**-**up****(3 months)**
Primary outcome measures			
Dynamic Gait Index	✓	✓	✓
Dizziness Handicap Inventory	✓	✓	✓
Secondary outcome measures			
Dizziness features	✓	✓	✓
Fall data	✓	✓	✓
ABC scale	✓	✓	✓
VADL	✓	✓	✓
TUG (simple–manual– cognitive)	✓	✓	✓
Sit-to-stand test	✓	✓	✓
Multidirectional functional reach test	✓	✓	✓
Hand-grip strength	✓	✓	✓
Static balance	✓	✓	✓
Geriatric Depression Scale	✓	✓	✓
Home exercise compliance data		✓	✓
Adherence/satisfaction with treatment		✓	✓
Characterization data			
Social and demographic data	✓		
Health status	✓	✓	✓
Anthropometric data	✓		
Mini-Mental State Examination	✓		
Follow-up questionnaire			✓

ABC, Activities-specific Balance Confidence Scale; TUG, Time Up and Go Test; VADL, Vestibular Disorders Activities of Daily Living Scale.

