### Sample size calculation

The estimated sample size was calculated considering previous DHI and DGI (primary outcomes) results based on a previously published trial
[25], which compared VR outcomes in young versus older adults with vestibular disorders. The *t* test was used to detect clinical difference between means of continuous variants (primary outcomes) with 80% power, and 5% significance level. Estimations indicated that 34 individuals were required for the DGI (effect size = 2.5; standard deviation = 3.5) and 32 individuals for the DHI assessments (effect size = 14; standard deviation = 20), where effect size is the mean difference expected between the two groups and standard deviation is for the population. Hence, a minimum of 68 patients will be necessary for the sample. To minimize the effects of the dropout rate, at least 15% more individuals will be required to compose the final sample.

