### Interventions

Interventions will be performed according to two distinct VR protocols (conventional Cawthorne&Cooksey and multimodal Cawthorne&Cooksey) conducted in the Otoneurology outpatient clinic. The VRs will be provided by two physiotherapists experienced in balance rehabilitation of older individuals and trained to standardize the VR protocols.

The control group will receive an active treatment, since scientific benefits of VR are already in evidence. In this case, placebo or nontreatment groups are not ethically advisable
[45]. The control group subjects will thus be treated according to the conventional Cawthorne&Cooksey VR protocol
[46-48], and the intervention group will be submitted to a novel protocol that includes multiple components to the conventional one.

The VR protocols will be provided in individual 50-minute sessions, twice a week, for 2 months (a total of 16 sessions). Under the condition of nonattendance, the session will be rescheduled to be performed in the same week. In the event of three (random or consecutive) absences during treatment, the subject will be excluded from the research and regarded as a withdrawal. In each session, absences, adverse symptoms, falling events, dizziness status according to the visual analog scale, and home exercises control will be recorded.

Regardless of the group, the subjects will be advised to maintain their usual activities and additional medical treatments during the research period. At the first session of both protocols, the subjects will receive a booklet including general information about VR, dietary advice, fall prevention and home exercises. The home exercises should be performed daily and consist of head and eye movements, performed while lying down (seven exercises, 14 minutes) and sitting (seven exercises, 14 minutes) to assure the patients’ safety. Following the recommendations, the intervention protocols will be implemented according to the randomization procedure.

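### The only recall period given for falls is 6 months; if used at the 8-week and follow-up visits, it reaches back before randomisation and dilutes any difference between arms

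*Protocol article*

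**What the plan says.** Outcome measures places fall data among the secondary outcomes, with two components and one recall period: "Fall data will include the history of falls in the previous 6 months and fear of falling". On timing, the same section says "Older patients will be submitted to baseline assessment (prior to randomization), and will be retested at post-treatment (8 weeks) and follow-up (3 months". Table 1 ticks the fall-data row at all three visits, under secondary outcomes rather than under the data that characterise the sample. No other recall period is given.

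Methods/design says "This is a randomized, single-blind, controlled clinical trial with a 3 months follow-up period", without saying when the 3 months begin. Interventions gives the treatment period: "The VR protocols will be provided in individual 50-minute sessions, twice a week, for 2 months (a total of 16 sessions". That section also provides a second source of fall data: "In each session, absences, adverse symptoms, falling events, dizziness status according to the visual analog scale, and home exercises control will be recorded".

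Statistical analysis compares outcomes across the three visits by repeated-measures analysis of variance and fills a missing retest with the last available value. Background expects the multimodal protocol to improve independence and balance and "as a consequence may reduce falls"; the Discussion also mentions preventing falls. The stated aim names functional capacity and balance control, not falls. Trial status reports that the study was concluded by September 2012, with analysis to follow in 2013.

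**The concern.** A 6-month look-back suits a baseline visit. Asked 8 weeks after randomisation, it mostly returns falls that no treatment could have influenced. Those falls inflate the count in both arms and pull the ratio between arms towards one. The windows at successive visits also share many weeks, so the repeated-measures comparison partly sets the same falls against themselves. Carrying the last value forward adds to this: a participant who misses the 8-week visit would contribute a count taken wholly before randomisation as a post-treatment result.

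Fall reduction is one of the reasons offered for the multimodal protocol. The risk is that little or no difference in recalled falls at 8 weeks is read as evidence that the protocol does not affect falls, when the measure was poorly placed to show it.

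**Working it through.** **Plan's own figure.** The article gives no fall rate, effect or power for falls. Its sample size covers the two primary outcomes only, "with 80% power, and 5% significance level". A two-sided two-sample t test gives 32 per arm for the DGI inputs (2.5; 3.5) and 34 for the DHI inputs (14; 20). The larger, doubled, is 2 × 34 = 68, which matches the stated total. (The article attaches 34 to the DGI and 32 to the DHI. The two look interchanged, with no effect on the total.) I use 34 per arm below.

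**Inputs.** From Outcome measures and Table 1: recall of 6 months, about 26 weeks; post-treatment visit at week 8; follow-up at 3 months, about 13 weeks. The follow-up visit is therefore at week 13 if counted from baseline, or 8 + 13 = week 21 if counted from the end of treatment. My assumptions: baseline, randomisation and start of treatment coincide at week 0; the fall rate is constant; recall is accurate; the full effect starts at week 0; true rate ratios are 0.50 and 0.70.

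**Step 1: share of the window before randomisation** = (26 − t)/26.

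**Step 2: apparent ratio** = pre-share + (1 − pre-share) × true ratio.

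| Visit | Pre-share | True 0.50 appears as | True 0.70 appears as |
|---|---|---|---|
| Week 8 | 18/26 = 69% | 0.692 + 0.308 × 0.50 = 0.85 | 0.692 + 0.308 × 0.70 = 0.91 |
| Follow-up, week 13 | 13/26 = 50% | 0.50 + 0.50 × 0.50 = 0.75 | 0.50 + 0.50 × 0.70 = 0.85 |
| Follow-up, week 21 | 5/26 = 19% | 0.192 + 0.808 × 0.50 = 0.60 | 0.192 + 0.808 × 0.70 = 0.76 |

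**Step 3: overlap.** The windows are weeks −26 to 0 at baseline, −18 to 8 at post-treatment, and −13 to 13 or −5 to 21 at follow-up. Baseline and week 8 share 18 weeks. Week 8 and follow-up share 21 weeks (follow-up at week 13) or 13 weeks (at week 21). All three share 13 or 5 weeks, and a fall in that stretch counts at every visit.

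**Step 4: illustration of power.** Poisson counts, 34 per arm, true ratio 0.50, and an assumed 0.3 to 1.0 falls per person per 6 months. With m1 and m2 the expected falls per person in each arm, power = Φ(|ln(m2/m1)|/SE − 1.96), where SE = √(1/(34·m1) + 1/(34·m2)). These runs used 26.09 weeks for 6 months.

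Example at week 8 with 1.0 fall per 6 months:
- 6-month window: m1 = 1.0, m2 = 0.847, SE = 0.253, power = Φ(0.166/0.253 − 1.96) = 9.6%.
- Counting from randomisation: m1 = 0.307, m2 = 0.153, SE = 0.536, power = Φ(0.693/0.536 − 1.96) = 25.2%.

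| Visit | 6-month window | Since randomisation |
|---|---|---|
| Week 8 | 5.5% to 9.6% | 10.5% to 25.2% |
| Week 13 | 8.7% to 19.4% | 14.5% to 37.8% |
| Week 21 | 17.1% to 45.2% | 20.8% to 55.4% |

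The shorter window counts fewer falls but keeps the full contrast, and on these assumptions it gives more power at every visit. If counts vary more than Poisson, all these figures are optimistic.

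**The case against.** **Repetition of the window is inferred.** No sentence says the 6-month question is put again at the retests. Table 1 ticks a composite row, and fear of falling alone could justify the later ticks. The row for dizziness features is also ticked three times although it includes etiology and time since first occurrence, which are not measures of response. A condensed article may omit visit-specific wording. This stands, so the point is conditional. It remains more than missing detail, because the only window the text attaches to this outcome is the 6-month one.

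**A reader might infer that any effect on falls is hidden, or that the outcome is mostly pre-treatment history throughout.** The documents support neither. The ratio is diluted, not set to one. The pre-randomisation share is a majority only at 8 weeks; at follow-up it is half or about a fifth. Falling events are also recorded at sessions. Those records only partly answer the problem, however: they stop when sessions stop, and the article does not make them the fall outcome or say whether they cover falls between sessions.

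**Pre-randomisation falls favour neither arm.** Correct. They balance in expectation, so the expected difference in number of falls is unchanged. They still shrink the ratio and add noise.

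**Falls are secondary and unpowered.** Also correct. Even with a corrected window, the illustration gives 10.5% to 25.2% power at 8 weeks. A null result would be weak evidence in any case, so the window is not its sole weakness. That limits the importance of the point but is no reason to dilute further.

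**Conclusion.** The point holds in a conditional form. If the one stated recall period is used at each scheduled visit, 69% of it precedes randomisation at 8 weeks, and 19% or 50% at follow-up depending on an origin the article leaves open. Successive windows overlap. A true ratio of 0.50 would be expected to appear as about 0.85 at 8 weeks and as 0.60 to 0.75 at follow-up; a true 0.70 as about 0.91, and as 0.76 to 0.85.

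The shares follow from the stated times, with week 0 taken as both baseline and randomisation. The diluted ratios rest on a constant fall rate, full effect from week 0 and assumed true ratios, since the article gives none. Fear of falling and the primary outcomes are untouched. The bias is towards no difference, so the main danger is a misleading null statement about falls, chiefly at 8 weeks.

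**What to change.** **In the plan.** Keep the 6-month recall for baseline only. Define the retest outcome as falls since the previous visit; the two retest reports then add up to falls since randomisation without double counting. Compare arms over time at risk, adjusted for baseline falls. Say when the 3 months of follow-up begin, and how the session records are used.

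**With data collection closed, as Trial status indicates.** Rewording the question is no longer possible, so if the 6-month question was asked at the retests:
- Do not interpret the 8-week 6-month recall as a treatment effect.
- Report falls recorded at sessions as the on-treatment measure, after confirming whether they include falls between sessions. State two limits: the Blinding section says therapists are not blinded, and they presumably keep these records (the recorder is not named); and the records end when a participant is withdrawn, which Interventions requires after three absences.
- For follow-up, state the origin of the 3 months and the share of the recall that precedes randomisation beside any result.

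If the forms did use a visit-specific window, one sentence saying so settles the matter.

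**Cost.** Before data collection, one reworded question. Now, a few sentences and an analysis of records already kept. The shorter window counts fewer events, and falls stay an unpowered secondary outcome, so the results should be presented as descriptive.

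### Adverse events are a stated aim but are recorded at treatment sessions, so events that stop a patient from returning can be missed

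*Protocol article*

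**What the plan says.** All references are to the protocol article.

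- **Aim of the proposed study** sets the objective: "Secondarily, this clinical trial intends to report sample withdrawals, adverse events and session-to-session VR progress".
- **Outcome measures** says when adverse effects are captured: "Finally, adherence and adverse effects will also be recorded during the treatment sessions".
- **Interventions** says the same in more detail: "In each session, absences, adverse symptoms, falling events, dizziness status according to the visual analog scale, and home exercises control will be recorded".
- **Interventions** also gives two attendance rules. For a missed session: "Under the condition of nonattendance, the session will be rescheduled to be performed in the same week". For repeated absence: "In the event of three (random or consecutive) absences during treatment, the subject will be excluded from the research and regarded as a withdrawal".
- **Table 1** lists what is measured at baseline, 8 weeks and 3 months. It has no adverse-event row. Dizziness features, fall data and health status appear at all three time points.
- **Outcome measures** describes a follow-up questionnaire, placed in Table 1 at 3 months only. Besides satisfaction with treatment it covers "hospitalization, unexpected clinical appointments, change in medication, use of medication for dizziness, new clinical diagnosis, occurrence of negative events in life", and its stated purpose is "in order to detect possible problems that could interfere in the VR results in the long term".
- **Statistical analysis** carries earlier values forward for non-completers in the intention-to-treat analysis and leaves excluded subjects out of the per-protocol analysis.

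**The concern.** Where adverse events are recorded at sessions, recording depends on attendance, and an event can itself end attendance. A patient who stops coming after a bad reaction, an injury or marked worsening is the patient whose event matters most to the stated aim. Under the written rules, session recording stops for that patient. The absence is noted, but the article describes no enquiry into its cause. Such a patient could be missing from the event count and also enter the intention-to-treat analysis as unchanged.

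Two things are at stake. The first is the absolute number of patients with an event, which would be too low. The second is the comparison of the protocols. The multimodal protocol keeps all the conventional exercises and adds flexibility, cognition, sensory-interaction and strength components that are meant to be functionally more demanding. Participants are aged 65 or over, and other disabling disease does not exclude them. Tolerability could differ between the arms, so loss of events could differ too.

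**Working it through.** **1. What each source can capture, and for whom**

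| Source | When | Whom it reaches | Limit as an adverse-event record |
|---|---|---|---|
| Session record | Each session | Patients who attend, including at a rescheduled session | Ends when the patient stops coming or is excluded |
| Dizziness features | 8 weeks, 3 months | Those assessed | Measures symptom state, not events linked to treatment |
| Fall data | 8 weeks, 3 months | Those assessed | Six-month recall: at 8 weeks it reaches back about 4 months before treatment began |
| Health status | 8 weeks, 3 months | Those assessed | Diseases, medication, cane use, pain, smoking; listed as characterisation data |
| Follow-up questionnaire | 3 months, once | Those assessed | Written to find influences on the long-term results |

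The article does not say whether patients excluded for absence attend the 8-week and 3-month assessments. If they do, part of the loss is recovered. If they do not, the session record up to their last attendance is all there is.

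**2. Plan figures that bear on size**

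The article gives no adverse-event rate and no absence rate by arm, so there is no stated figure to reproduce for this point. The planned dropout allowance gives a scale. The minimum sample is 68 = 2 × 34, with at least 15% more to be recruited:

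- 68 × 1.15 = 78.2, so 79 patients, an allowance of 79 − 68 = 11;
- 68 / 0.85 = 80 patients, an allowance of 80 − 68 = 12.

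The plan thus allows for about 11 or 12 patients lost across both arms. If losses stay within that allowance, this is also the most patients whose events could be missed through non-return. The true figure would be smaller, because some leave for unrelated reasons and some have an event recorded before they leave.

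**3. Effect on the arm comparison (assumed rates)**

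Observed risk = true risk × (1 − share of affected patients who never return).

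Assume true risks of 30% (multimodal) and 20% (conventional), a true ratio of 0.30 / 0.20 = 1.5. The last column is the number of patients with a missed event at 40 per arm: 40 × true risk × share lost, summed over the arms.

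| Share lost, multimodal / conventional | Observed risks | Observed ratio | Patients missed |
|---|---|---|---|
| 10% / 10% | 27% / 18% | 1.50 | 1.2 + 0.8 = 2.0 |
| 20% / 20% | 24% / 16% | 1.50 | 2.4 + 1.6 = 4.0 |
| 20% / 10% | 24% / 18% | 1.33 | 2.4 + 0.8 = 3.2 |
| one third / 0% | 20% / 20% | 1.00 | 4.0 + 0 = 4.0 |
| 50% / 10% | 15% / 18% | 0.83 | 6.0 + 0.8 = 6.8 |

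Two results follow. Every row understates the risk in at least one arm, and the ratio moves only when the shares lost differ. All rows, including the reversal in the last, need fewer missed patients than the planned allowance of 11 or 12. The unequal-loss rows are therefore possible within the plan's own dropout figure, but nothing in the article shows that they are likely.

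**The case against.** The case on the other side is substantial, and several parts of it stand.

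- **Capture is not confined to sessions.** Missed sessions are rescheduled within the week, so a patient who returns can report an event within days. Falls, pain, medication and dizziness are asked again at 8 weeks and 3 months, and hospitalisation and new diagnoses at 3 months. This stands. It narrows the gap to patients who do not return, but does not close it, because the article nowhere says that excluded patients are asked.
- **A condensed article may leave adverse-event forms, reasons for absence and contact with dropouts to the full protocol.** This stands for detail. It does not remove the point, which rests on stated rules: recording placed at sessions, a measurement schedule without an adverse-event row, and exclusion after three absences.
- **The direction of any bias is unknown.** This stands. A reader might infer that the protocol patients tolerate worse will look safer than it is. The article does not support that as a statement of fact. It would need non-return after an event to differ by arm, and equal loss leaves the ratio unchanged. Exercises are also to be adjusted to individual tolerance in the standard protocol, and an arm that drives patients away would show more withdrawals, which the trial intends to report.
- **No test of safety between arms is described, and the trial is small.** This stands as well. With 34 per arm, fully recorded counts of 7 against 3 would give a Fisher exact p of 0.30. The harm lies in the description of events by arm rather than in a formal test.
- **The study is over.** The Trial status section says it was concluded by September 2012, which limits what can still be changed.

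**Conclusion.** The point holds in a limited form. Adverse events are a stated secondary aim, the only recording described for them is at treatment sessions, and the three-absence rule ends that recording. Events that stop a patient from returning can be missed, and absolute counts would then be too low. If losses stay within the plan's allowance, at most about 11 or 12 patients are affected. A distorted comparison between arms is possible but not shown: in the illustration the ratio of 1.5 stays at 1.5 under equal loss, falls to 1.33 at 20% against 10% lost, and reaches 1.0 at one third against none. The risks and shares lost are assumptions, since the article gives neither.

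It would go too far to say that events outside sessions are never counted, or that the withdrawal report cannot separate harm from other reasons. The article describes partial later capture, and it does not say that reasons go unrecorded. The primary outcomes' definitions are not affected. The change is worth making because it serves a declared aim at little cost.

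**What to change.** For the plan:

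1. Put one standard adverse-event question to every randomised patient at 8 weeks and at follow-up, including those excluded for absence, by telephone if they no longer attend. Add the row to Table 1. The three-absence rule itself need not change for this.
2. Record the reason for each absence and each withdrawal.
3. Report, by arm, the number of patients with at least one event over the number randomised, and withdrawals by reason.

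The cost is a few minutes of contact for each absent or withdrawn patient and one question at two existing time points. Some withdrawn patients will not be reached; their number by arm should be given.

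Because the study has concluded, prospective collection may no longer be possible. At minimum, the report should give withdrawals by arm with the reasons that are known, give events per randomised patient by arm, and state that adverse events were ascertained mainly at attended sessions. This needs no new data.
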